## Abstract

**Background:** Age-related declines in physical function lead to decreased independence and higher healthcare costs. Individuals who meet the endurance and resistance exercise recommendations can improve their physical function and overall fitness, even into their ninth decade. However, most older adults do not exercise regularly, and the majority of those who do only perform one type of exercise, and in doing so are not getting the benefits of endurance or resistance exercise. Herein we present the study protocol for a randomized clinical trial that will investigate the potential for high-intensity interval training (HIIT) to improve maximal oxygen consumption, muscular power, and muscle volume (primary outcomes), as well as body composition, 6-min walk distance, and muscular strength and endurance (secondary outcomes).

**Methods and Analysis:** This is a single-site, single-blinded, randomized clinical trial. A minimum of 24 and maximum of 30 subjects aged 60–75 that are generally healthy but insufficiently active will be randomized. After completion of baseline assessments, participants will be randomized in a 1:1:1 ratio to participate in one of three 12-week exercise programs: stationary bicycle HIIT, stationary bicycle moderate-intensity continuous training (MICT), or resistance training. Repeat assessments will be taken immediately post intervention.

**Discussion:** This study will examine the potential for stationary bicycle HIIT to result in both cardiorespiratory and muscular adaptations in older adults. The results will provide important insights into the effectiveness of interval training, and potentially support a shift from volume-driven to intensity-driven exercise strategies for older adults.

**Clinical Trial Registration:** This trial is registered with ClinicalTrials.gov (registration number: NCT03978572, date of registration June 7, 2019).

## Introduction

Nearly half of US adults over age 60 report difficulty performing one or more activities of daily living essential to maintaining independence, a fraction that has remained stable over the last 20 years despite an overall increase in the mean age of the US population (1). Increasing numbers of older adults with disabilities will continue to drive up healthcare costs, making maintenance of health and independence a top priority for both middle-aged and older adults (2). Contributors to this functional decline include poor cardiorespiratory fitness and skeletal muscle impairments (3–5), which can partially be attributed to reduced physical activity with age (6–8). Exercise is effective at maintaining function in older adults, as evidenced by data indicating those who take part in supervised exercise programs demonstrate improvements in functional outcomes (9–11). The fact that adaptations have been seen in the oldest adults (90+ years) is particularly encouraging (12–14).

Unfortunately, <12% of older adults meet the exercise recommendations provided by the American College of Sports Medicine (ACSM) (1, 15). These recommendations include weekly accumulation of at least 150 min of moderate intensity aerobic activity or 75 min of vigorous aerobic (endurance) activity, and at least 2 days of resistance exercise to improve muscular endurance, power, and strength (15). In 2014, 36.5% of adults over the age of 65 met the aerobic exercise recommendations, while only 16.5% met the resistance exercise recommendations; only 11.7% met both aerobic and resistance recommendations simultaneously (1). Consequently, the majority of older adults who do exercise are either not getting the muscular adaptations necessary for maintaining independence, or they are not getting the necessary cardiorespiratory adaptations. However, certain types of exercise may be able to induce both cardiorespiratory and muscular adaptations in older adults.

Resistance exercise appears to have minor effects on cardiovascular disease (CVD) risk factors, though its benefits include the prevention of musculoskeletal injuries, muscle wasting, and impairments in physical function (16). On the other hand, aerobic exercise is effective at reducing CVD risk by improving heart, lung, and metabolic function, though it appears to have little effect on muscular properties (17). However, recent work indicates that the absence of muscular adaptations in response to aerobic training may be related to exercise intensity and mode of exercise (18, 19). The most popular form of physical activity in older adults is walking, and recommendations for older adults promote walking as the primary means to increase physical activity levels (15, 20, 21). While walking may challenge older adults and result in cardiovascular improvements, the relatively low intensity of muscular contractions would be unlikely to elicit hypertrophy or functional adaptations of the leg muscles (22). Even higher intensity running does not seem to result in increased muscle size or strength (19, 23), and running may blunt the muscular benefits of resistance training when performed concurrently (24). In contrast, stationary bicycle training can increase muscular strength and size (25–27), and does not seem to interfere with the muscular adaptations to resistance training (24). Bicycle high-intensity interval training (HIIT) in particular may be the ideal form of aerobic exercise able to elicit muscular adaptations. Young adults performing bicycle HIIT demonstrate improved muscle strength (28) and power (29, 30), along with enhanced cardiorespiratory function (31).

HIIT has gained popularity in recent years, with most research in middle-aged and older cardiac rehabilitation patients (32, 33). Compared to traditional aerobic training, HIIT typically has a greater effect on VO_2_max (9.1% greater increase on average) and other CVD risk factors (e.g., cholesterol, blood pressure) (33). While its success in rehabilitation is encouraging, the effectiveness of HIIT as a general exercise strategy for older adults has not been adequately investigated, with few studies reporting physiological adaptations to HIIT in older adults (33–44). Furthermore, limitations make it difficult to generalize these studies to a healthy aging population. Specifically, these studies have had one or more of the following methodological confounds:

They lacked an active control group that followed established exercise recommendations.They were short-term interventions.The target population had overt diseases/health conditions, which may limit generalizability to the large number of older adults that are generally healthy.

The lack of investigations that directly compare unique exercise strategies against established strategies represents a critical barrier to progress in the field of healthy aging. With this in mind, the DART Study (Dual-benefits of Aerobic and Resistance Training) is a phase 1B proof-of-concept, proof-of mechanism clinical trial that seeks to determine if bicycle HIIT is a more efficient standalone strategy to improve cardiovascular and lower extremity muscular function than established resistance or aerobic exercise training programs. We will test this “dual-benefits hypothesis” in generally healthy older adults that have yet to develop mobility limitations, but who, without intervention, could very likely develop mobility limitations in the future due to inactivity and normal time course of aging.

## Methods and Analysis

### Design

This is a single-blinded (outcomes assessor), single-site, randomized control trial. It is a three (group) by two (time) repeated measures factorial design. The overall study is illustrated in Figure 1.

**Figure 1 F1:**
[figure not shown]
Detailed overview of DART Study protocol. DBP, diastolic blood pressure; DXA, dual-energy X-ray absorptiometry; GXT, graded exercise test; HIIT, high-intensity interval training; Hx, history; MICT, moderate-intensity continuous training; MRI, magnetic resonance imaging; RT, resistance training; SBP, systolic blood pressure; SPPB, short physical performance battery; TRFD, twitch-evoked rate of force development; VRFD, voluntary rate of force development.

### Study Subjects

A minimum of 24 (and up to 30) subjects aged 60–75 years of age that are generally healthy but sedentary will be recruited, enrolled, and randomized in this study (*n* = 8–10 per group). Potential subjects will be recruited from the local community by way of flyers, community events, or emails to individuals who have previously participated in studies with the Ohio Musculoskeletal and Neurological Institute at Ohio University in Athens, Ohio, USA. All interested individuals will complete a pre-screening phone interview, and all that are not ruled ineligible will be invited for in-person screening. Written informed consent will be obtained from each subject in accordance with the Declaration of Helsinki. Ethical Approval for this study has been obtained from the Ohio University Institutional Review Board (protocol number 18-F-55).

Eligible subjects will be insufficiently active. We define “insufficiently active” as not meeting either the endurance or resistance exercise recommendations for older adults, as set forth by the American College of Sports Medicine (ACSM), for three consecutive months. The current ACSM recommendations for endurance training are 150–300 min per week of moderate-intensity activity (perceived exertion of 5–6 on 0–10 scale), or 75–150 min per week of vigorous-intensity activities (perceived exertion of 7–8 on 0–10 scale) (15). The recommendations for resistance training are at least 2 days per week of progressive weight training activities that use the major muscle groups (perceived exertion of 5–8 on 0–10 scale) (15). Additionally, the subjects must not be highly active outside of a structured exercise program (i.e., consistent hard physical labor). They must also have a 6-min walk distance within a normal range for adults aged 60–75. We calculated a normal 6-min walk range by averaging 6-min walk values from multiple studies, plus or minus one standard deviation (45–48). The calculated 6-min walk range for females was 400–675 meters, and for males was 450–725 meters. Table 1 describes inclusion and exclusion criteria in detail. These criteria are designed to recruit a generally healthy, but insufficiently active population, and exclude individuals with poor health and physical function where there could be concerns about a subject's ability to appropriately perform the testing and exercise prescription.

**Table 1 T1:** Inclusion and exclusion criteria.

Inclusion Criteria: •Age 60–75 years with no significant health issues or conditions that, in the investigators' opinion, would limit the subject's ability to complete the study per protocol or that would impact the capability to get an accurate measurement of study endpoints. •Body mass index between 18 and 40 kg/m^2^. •Willingness to maintain current diet and adhere to the intervention programs described for the study and willing to undergo all testing procedures. •Able to read, understand, and complete study-related questionnaires. •Able to read and understand, and willing to sign the informed consent form (ICF). •Six-min walk distance of 450–725 meters for men and 400–675 meters for women.Exclusion Criteria: •Short physical performance batter (SPPB) score <8. •Any activities of daily living disability (difficulty feeding, dressing, continence, bathing, toileting, and transferring). •Lives in a nursing home or assisted living facility. •Known neuromuscular or neurological conditions affecting somatosensory or motor function or control (e.g., hemiplegia, multiple sclerosis, peripheral neuropathy, Parkinson's disease, Myasthenia Gravis, Ataxia, Apraxia, post-polio syndrome, mitochondrial myopathy, etc.). •Unable to communicate because of severe hearing loss or speech disorder. •Severe visual impairment, which would preclude completion of the assessments. •Cancer requiring treatment currently or in the past 2 years (except primary non-melanoma skin cancer or *in situ* cervical cancer). •Hospitalization (medical confinement for 24 h), or immobilization, or major surgical procedure requiring general anesthesia within 12 weeks prior to screening, or any planned surgical procedures during the study period. •Chronic or relapsing/remitting gastrointestinal disorders such as inflammatory bowel disease and irritable bowel syndrome. •Known history of human immunodeficiency virus (HIV) antibody at screening. •Use of systemic glucocorticoids. •Any history of angina pectoris. •Any history of heart failure. •Any history of myocardial infarction. •Any coronary artery bypass graft or percutaneous coronary intervention. •Heart disease that limits exercise (valvular, congenital, ischemic, and hypertrophic cardiomyopathy). •Complex ventricular arrhythmias or heart block. •Chronic obstructive pulmonary disease, cerebrovascular disease, or peripheral vascular disease. •Diabetes mellitus •Severe neuropathy. •Mini-mental state exam score below 19. •Psychiatric conditions that warrant acute or chronic therapeutic intervention (e.g., major depressive disorder, bipolar disorder, panic disorder, schizophrenia) that in the investigators' opinion may interfere with the conduct of study procedures. •Unable to undergo magnetic resonance imaging (MRI) (e. g., body containing any metallic medical devices or equipment, including heart pacemakers, metal prostheses, implants or surgical clips, any prior injury from shrapnel or grinding metal, exposure to metallic dusts, metallic shavings or having tattoos containing metallic dyes). •Unable to reliably undergo exercise or strength tests described for this study. •Participation in progressive resistance exercise 2 or more days/week for most weeks over the 24 weeks prior to screening, OR 150+ min of accumulated aerobic exercise each week for most weeks over the 24 weeks prior to screening. •Current self-reported activity level that, in the investigators' opinion, is considered highly active for older adults. •Participation in any clinical trial within 12 weeks prior to screening. •Limb amputation (except for toes). •Bone fracture within 24 weeks prior to screening. •Any disorder that will not allow completion of the motions required for resistance or aerobic exercise. •Conditions (such as myasthenia gravis, myositis, muscular dystrophy, or myopathy, including drug-induced myopathy) leading to muscle loss, muscle weakness, muscle cramps, or myalgia. •Acute viral or bacterial upper or lower respiratory infection at screening. •Abnormal or uncontrolled blood pressure (BP) at the screening visit defined as BP > 170/100 mmHg. If taking anti-hypertensive medication, have to be on stable doses of medication for more than 3 months. •Current or recent history (within 1 year of screen) of heavy alcohol consumption or drug abuse that in the investigators' opinion may interfere with the conduct of study procedures. •Reports being pregnant, lactating, or that they anticipate becoming pregnant in the next 3-months. If a woman becomes pregnant while on study protocol, they will be withdrawn from the study. Prohibited Medications: Medications that, in the PIs opinion, would confound study integrity by interacting with study outcomes. For instance: •Anti-obesity drugs, nutraceuticals, and dietary supplements that may affect body mass and body composition. •Any drug or supplement known to influence muscle mass or performance including but not limited to anabolic steroids, insulin-like growth factor 1, growth hormone, replacement androgen therapy, anti-androgen therapy.

### Randomization

Subjects will be randomized in a 1:1:1 ratio to receive a 12-week exercise program consisting of either resistance training (RT), moderate-intensity continuous training (MICT) on a stationary bicycle, or HIIT on a stationary bicycle. Due to the small sample size in each arm, permuted-block randomization will be used via computer-generated random numbers to ensure equal sample size. Specifically, we will create blocks of three with each treatment permuted within each block. The study subjects will be enrolled and assigned to their respective interventions by an unblinded project manager.

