#### Implementation

The allocation sequence will be generated by a biostatistician. Subjects will be enrolled in the study and assigned to their intervention group by the project manager.

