#### Blinding

Due to the nature of the intervention neither subjects nor staff can be blinded to allocation. The outcomes assessor and data analyst will be blinded after study completion by having the subjects' demographic and intervention group information coded.

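### Fixed blocks of three, with an unblinded project manager who both enrols and assigns, make one third of allocations certain in advance: an avoidable opening for selection bias

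*Protocol article*

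**What the plan says.** All of this is in the protocol article, Methods and Analysis.

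- **Randomization.** "Subjects will be randomized in a 1:1:1 ratio to receive a 12-week exercise program". The reason for blocking is the small arms: "permuted-block randomization will be used via computer-generated random numbers to ensure equal sample size". The rule is then made specific: "we will create blocks of three with each treatment permuted within each block". No other block size and no stratification factor is mentioned.
- **Who acts.** The same section says subjects are "enrolled and assigned to their respective interventions by an unblinded project manager". Implementation repeats it: "Subjects will be enrolled in the study and assigned to their intervention group by the project manager". It gives list generation to someone else: "The allocation sequence will be generated by a biostatistician".
- **Blinding.** "Due to the nature of the intervention neither subjects nor staff can be blinded to allocation". Only the outcomes assessor and the data analyst are to be blinded, by coding.
- **Setting and timing.** Design describes a single site. Study Subjects gives 24 to 30 subjects, 8 to 10 per group. Study Timeline and Table 2 place randomization at Visit 3, after the baseline assessments, within a baseline period of at most 21 days.

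**The concern.** Permuted blocks protect balance at the price of predictability, and the price is highest when the block is as small as the number of arms. Here the block size is stated, there is one site with no stated strata and hence one sequence, and the person who enrols also makes, and therefore sees, every assignment. Concealing the list does not help, because the last place in each block follows from the two before it.

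Foreknowledge matters only if someone can act on it. Two routes are visible:

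- **Late exclusions.** Table 1 contains items left to the investigators' opinion and one on being unable to undergo the tests reliably. The Discussion adds exclusion for specified irregular cardiac responses at the baseline exercise test.
- **Order of entry.** Table 2 lets Visit 3 fall anywhere from day −17 to day −1, so when baseline periods overlap, the order in which people are randomized can shift.

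With 8 to 10 per arm, a few influenced placements carry weight. Blinded outcome assessment does not guard against this, because selection acts before the outcome is measured.

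**Working it through.** **Inputs.** Three arms, 1:1:1, blocks of three (Randomization); N = 24 to 30 (Study Subjects); one sequence (single site, no strata stated); all past assignments visible to the assigner (Randomization, Implementation, Blinding).

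**The plan's own figure.** 24/3 = 8 blocks and 30/3 = 10 blocks, one subject per arm per block. This gives 8 to 10 per group, as stated.

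**Predictability of blocks of three.** The chance of guessing the first place is 1/3, the second 1/2, the third 1.

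- Mean: (1/3 + 1/2 + 1)/3 = 11/18 = 61.1%.
- Expected correct guesses: 24 × 11/18 = 14.7; 30 × 11/18 = 18.3. Simple randomization gives 24/3 = 8 and 30/3 = 10 (33.3%).
- Certain beforehand: one per block, so 8 of 24 or 10 of 30. The same number again are 50:50.

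**Alternatives.** These were simulated with a guesser who knows the possible block sizes and all past assignments and always picks the most probable arm (3,000 runs; 6,000 for the scheme proposed under the fix). The alternative sizes are illustrations, not taken from the protocol.

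| Scheme | Correct guesses, N = 24 / 30 | Certain allocations, N = 24 / 30 |
|---|---|---|
| Fixed 3 (the plan) | 61.1% / 61.1% | 8 / 10 |
| Fixed 6 | 56.1% / 56.0% | 4.8 / 6.0 |
| Random mix of 3 and 6 | 57.3% / 57.4% | 1.9 / 2.5 |
| Random mix of 3, 6 and 9 | 54.5% / 54.7% | 0.8 / 1.1 |
| Random mix of 6 and 9 | 53.2% / 53.4% | 1.2 / 1.5 |
| 6, 9, 9 in random order (then 6) | 54.0% / 54.4% | 1.7 / 1.7 |
| Simple randomization | 33.3% | 0 |

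If the guesser also knew the exact make-up of the 6, 9, 9 (then 6) scheme, the guess rate would be the same, but 2.5 of 24 or 3.7 of 30 allocations would be certain. The sizes therefore have to stay undisclosed.

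**How large could the effect on outcomes be?** No bias in the outcome follows from a guess rate. As a bound, suppose no true effect, n = 8 per arm, and k subjects steered into one arm. To shift that arm's mean by D points, each must exceed the average response by 8D/k. Differences and SDs are those in Sample Size.

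- Thigh CSA, D = 6, SD 4: k = 2 needs 48/2 = 24 points (6 SD) each; k = 3 needs 48/3 = 16 points (4 SD) each.
- CSA with three steered in each of two arms, in opposite directions: each arm must move 3 points, so 24/3 = 8 points (2 SD) each.
- VO2max, HIIT against MICT, D = 32 − 15 = 17, SD 14: k = 3 needs 136/3 = 45 points (3.2 SD) each.
- VO2max, MICT against RT, D = 15 − 10 = 5: k = 3 needs 40/3 = 13.3 points (about 1 SD) each.

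The large planned contrasts are out of reach of a few steered subjects. The smallest is not.

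**The case against.** The strongest reply accepts the arithmetic and disputes the consequence.

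1. **Harm.** A reader might infer that two or three steered subjects could create the differences the trial is looking for. The protocol's figures do not support that: it would take 4 to 6 SD per subject for thigh CSA and more than 3 SD for HIIT against MICT on VO2max. The endpoints are also changes from baseline, so placing fitter people in an arm does not carry straight through; one would have to foresee who responds to training. This stands. Smaller shifts remain possible, and they matter for the smaller VO2max contrast and for a hypothesis that expects HIIT to equal MICT on endurance and RT on muscle.
2. **Route.** Study Timeline settles eligibility mainly at Visit 1, before anyone need know which place a person will take. The judgement items are attributed to the investigators, not to the project manager, and no passage says who schedules Visit 3. This also stands. What remains is late discretion and the order of randomization among people already enrolled.
3. **Missing detail.** A reader might fault the article for not saying how the list is held or released. An article may leave that to the full protocol, so it is no finding. The block size and the combined role are different: both are stated, and predictability follows from them whatever the concealment.
4. **Trade-off.** Small blocks were chosen to keep arms equal, and varying them only lowers the guess rate from 61% to about 53–54%. True, but the number of certain allocations falls much further, and sizes that sum to 24 and 30 keep the equality.
5. **Stakes.** This is a proof-of-concept trial whose p-values are to be read descriptively. That lowers the priority. It does not justify leaving an avoidable weakness in place.

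**Conclusion.** The point holds as a weakness of design with a bounded consequence. Under the stated rule, 8 of 24 (10 of 30) allocations are certain beforehand, as many again are 50:50, and the expected correct-guess rate is 61% against 33% by chance.

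This rests on three readings: that blocks are always of three (the only size named), that there is a single unstratified sequence, and that the project manager keeps track of past assignments. The first two follow from what the article states and does not qualify. The third follows from the role itself.

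The documents show an opportunity, not that anyone would use it, and they give no basis for a figure for bias in the outcomes. The change should be made, but the trial's validity does not turn on it.

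**What to change.** In Randomization, replace the fixed block size with a statement that block sizes vary in random order and are not disclosed to anyone who enrols or assigns. The biostatistician who already generates the list chooses them. One example is 6, 9 and 9 in random order, which gives 2 + 3 + 3 = 8 per arm at 24, with a further block of 6 giving 10 per arm at 30. The sizes actually used should not appear in the article.

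State also that each subject is assigned only after final eligibility has been confirmed at the end of Visit 3, so that no discretionary exclusion can follow knowledge of the arm. If randomization has begun, apply the change from the next block onward, with sizes that sum to the number still to be randomized.

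**Cost.** No extra staff. Arms are equal if enrolment stops at 24 or 30. Stopping inside a block of 9 can leave arms up to three subjects apart, and inside a block of 6 up to two; the present blocks of three allow at most one. Predictability is reduced, not abolished: about 53–54% of guesses would still be right, but with roughly one or two certain allocations in place of 8 to 10.
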